## Methods

### Trial Design

This study uses a randomized, double-blind, active-controlled (low-dose control), prospective, multicenter design. Eligible participants will be randomized in a 1:1 ratio to either the intervention group or the control group. Prior to enrollment, baseline data—including medical history, physical examination findings, relevant laboratory results, and patient-reported outcomes—will be collected for screening and eligibility confirmation. All enrolled participants will be managed under a unified protocol. The combined drug and psychological intervention will be administered over a 3-month period. On completion of the intervention, participants will undergo 3 subsequent follow-up visits, each spaced 3 months apart, resulting in a total follow-up duration of 12 months. Figure 1 presents the participant flow through the trial.

**Figure 1. F1:**
[figure not shown]
Study flowchart.

### Eligibility Criteria

#### Inclusion Criteria

The inclusion criteria are as follows:

Histologically or cytologically confirmed primary epithelial ovarian cancer.Meeting the diagnostic criteria for chronic insomnia defined by the Sleep Disorders Group of the Neurology Branch of the Chinese Medical Association, including a Pittsburgh Sleep Quality Index total score >8, a Piper Fatigue Scale total score >4, and a Patient Health Questionnaire-9 total score >5.Moderate-to-severe PNSC severity. PNSC will be assessed using the MDASI-OC. Moderate-to-severe PNSC is defined as a mean score of ≥4 across the 4 items: sleep disturbance, fatigue, distress, and sadness.Eastern Cooperative Oncology Group Performance Status score of 0 to 2.Age 18 to 70 years.Meeting the TCM diagnostic criteria for spleen-kidney yang deficiency syndrome.Expected survival >1 year.Signed informed consent form with voluntary acceptance of the treatment protocol and ability to independently complete sleep diaries.

#### Exclusion Criteria

The exclusion criteria are as follows:

Patients scheduled to undergo radiotherapy within the next 4 treatment cyclesComorbid severe primary diseases of the heart, brain, liver, kidney, or hematopoietic system, including hepatic dysfunction (aspartate aminotransferase or alanine aminotransferase >1.5 times the upper limit of normal) or renal impairment (serum creatinine >1.2 times the upper limit of normal)Pregnant or lactating women, individuals with psychiatric disorders (eg, schizophrenia, bipolar disorder, mania, depressive disorder, anxiety disorders, and phobias), intellectual or language impairments, or other mental health conditionsScores ≥15 on the Patient Health Questionnaire for depression or ≥15 on the Generalized Anxiety Disorder-7 at screeningPreexisting chronic insomnia or depression diagnosed prior to ovarian cancerComorbid autoimmune diseases, hematologic disorders, or long-term use of corticosteroids or immunosuppressantsHistory of other primary malignanciesParticipation in other clinical trials within 3 monthsHIV-positive status, congenital or acquired immunodeficiency disorders, or history of organ transplantation (including autologous bone marrow or peripheral stem cell transplantation)Legally incapacitated individuals or cases with medical or ethical contraindications to study continuationActive hepatitis B, active tuberculosis, or evidence of severe or uncontrolled systemic inflammatory conditions (eg, unstable respiratory, cardiovascular, hepatic, or renal diseases)Patients with diabetes

#### Dropout Criteria

The dropout criteria are as follows:

Occurrence of complications, comorbidities, or serious adverse events (SAEs) making continued participation in the trial inadvisable.Investigator determination that discontinuation or suspension of the clinical trial is warranted for safety reasons.Withdrawal from the study by the subject for any reason.Participants retain the right to withdraw from the trial at any time. Investigators should document the reason for withdrawal to the extent possible.

### Sample Size

A superiority design is used for this study. Given the lack of a universally established remission standard for the PNSCs derived from the MDASI-OC scale, parameters are determined based on internal pilot data and expert consensus. The remission rate for the control group at 3 months is estimated at 10%. We posited an absolute increase of 30% in the intervention group, corresponding to an expected remission rate of 40%. To ensure clinical significance, a superiority margin (*M*) of 15% is prespecified and incorporated into the sample size formula. Assuming a one-sided significance level (α) of .025 and a statistical power (1-β) of .80, calculations performed via PASS software (version 15.0; Superiority by a Margin Tests for the Difference Between Two Proportions) yielded a required sample size of 116 participants per group. Accounting for an anticipated 20% dropout rate, a minimum of 145 participants per group is required. To further enhance the robustness of the findings and to accommodate potential variability in dropout rates or covariate adjustments, the final total sample size is determined to be 316 participants (158 per group). This ensures that the actual statistical power of the final analysis set remains consistently above 80%.

### Randomization

After registration and completion of the baseline assessment, eligible patients who provide written informed consent will be randomly assigned in a 1:1 ratio to either the intervention group or the control group. Randomization will be performed using a centralized system using center-stratified block randomization. An independent statistician, who is not involved in the trial implementation, will generate the allocation sequence. The randomization results will be encrypted and transmitted to an independent third party responsible for the allocation system, where they will be kept confidential until trial completion. The personnel responsible for participant recruitment and intervention delivery will remain blinded to the group assignments.

### Blinding

This study adopts a double-blind design. Drug blinding and distribution packaging are jointly carried out by statisticians who are not directly involved in this clinical trial and the pharmaceutical factory responsible for drug production. The trial drug and the control drug are respectively assigned unique drug packaging numbers and drug blinding codes, which are filled in (or pasted) on the drug labels. The control drug contains 10% of the components of the investigational drug. This active-controlled design provides a more rigorous comparison and addresses the practical challenges of producing an indistinguishable placebo in TCM research.

An independent blind background file will be established for each random number. The content includes key information such as the group to which the subject with the number is assigned (such as group A or group B) and the medication requirements (investigational drug or control drug) in case of emergency unblinding. The third party responsible for the random system is responsible for confidential storage. It is only opened by authorized personnel in accordance with the procedures in emergency situations, such as SAE, where unblinding is necessary.

A 2-step unblinding method will be adopted. After all research data are entered, verified, and have undergone blinded review, the database will be locked. The first unblinding will be performed by the blinding code custodian to identify group A and group B. This information will then be handed over to the biostatistician for statistical analysis. After the statistical analysis is completed, the second unblinding will be conducted to clarify the intervention and control groups.

### Interventions

In this trial, both the intervention and control groups will receive standard-of-care treatment for ovarian cancer as the foundational therapy, in accordance with the 2024 NCCN International Guidelines. This may include platinum-based chemotherapy and/or targeted, antiangiogenic, or hormonal agents, as clinically indicated.

Both the intervention and control groups will receive the same psychological intervention. The intervention is based on CBT and mindfulness theory and is adaptively designed to address the characteristics of the PNSC in patients with ovarian cancer. It comprises a total of 12 sessions. The intervention is delivered in an online prerecorded format, once weekly, with each session lasting approximately 30 to 45 minutes. The materials are distributed to participants on schedule by the investigators according to a treatment manual. The session content includes cognitive restructuring of illness perceptions, pain tolerance, understanding and expressing interpersonal needs, family and social support, comorbidity of depression and sleep disturbances, sleep hygiene education, the theoretical basis of insomnia, stimulus control, cognitive restructuring for insomnia, emphasis on long-term coexistence, finding meaning within limitations, and relapse prevention. All sessions will be recorded by qualified mental health professionals from the Shanghai Mental Health Center, China. Prior to release, each session script is independently reviewed by another psychotherapist or the principal investigator to ensure objectivity, avoid leading statements or overpromising, and comply with ethical requirements for psychooncological interventions. To ensure consistency of intervention delivery across centers, standardized prerecorded materials are used at all sites. Investigators at each center receive unified training prior to study initiation, and intervention adherence is centrally monitored and recorded by the study team.

In addition, participants in the intervention group will receive the TSZA regimen, which consists of Compound Ciwujia Granules (containing *Acanthopanax senticosus* and *Schisandra chinensis*) combined with psychological intervention. The granules will be administered twice daily, one sachet each time, 30 to 60 minutes after meals, for a continuous period of 3 months.

The control group will receive matching low-dose active control granules (containing 10% of the active ingredients found in Compound Ciwujia Granules), which are identical in appearance, odor, and taste to the investigational drug, following the same dosing schedule.

During the study period, the use of any medications not specified in the study protocol is prohibited. In principle, participants should not take other Chinese herbal medicines, Chinese patent drugs with sedative or sleep-promoting claims, biologics, or any other agents that may potentially affect sleep, fatigue, or mental health. Any use must be reported.

### Follow-Up

During the 3-month treatment period, follow-up visits will be scheduled once per month. After the completion of treatment, follow-up assessments will be performed every 3 months. The total follow-up duration will be 1 year. Data collection time points are presented in Table 2.

**Table 2. T2:** Study timeline.

Study stage	Screening and baseline period	Treatment period			Follow-up period		
Visit (times)	0	1	2	3	4	5	6
Time point (day)	−14 to 0	30	60	90	180	270	360
Time window (day)	+3 or −3	+3 or −3	+3 or −3	+3 or −3	+7 or −7	+7 or −7	+7 or −7
Collection of basic medical history							
Informed consent	✓						
Emission standards	✓						
Demographic data	✓						
Diagnosis and treatment history	✓						
Assessments of validity							
MDASI-OC^a^ scale	✓	✓	✓	✓	✓	✓	✓
PSQI^b^ sleep scale	✓	✓	✓	✓	✓	✓	✓
PFS-R^c^ scale	✓	✓	✓	✓	✓	✓	✓
PHQ-9^d^ depression scale	✓	✓	✓	✓	✓	✓	✓
GAD-7^e^ anxiety scale	✓	✓	✓	✓	✓	✓	✓
EORTC QOL-C30^f^ scale	✓	✓	✓	✓	✓	✓	✓
TCM^g^ syndrome scale	✓	✓	✓	✓	✓	✓	✓
One-year OS^h^ rate and PFS^i^ rate							✓
Sleep quality	✓	✓	✓	✓			
Sleep diary	✓	✓	✓	✓			
fMRI^j^	✓			✓			
Biological targets in peripheral blood	✓			✓			
Biological targets in tumor tissue	✓						
Tumor markers	✓			✓			
Proportions of immune cells	✓			✓			
Cytokine levels	✓			✓			
HPA^k^ axis function	✓			✓			
Analysis of immune gene expression	✓			✓			
Vital signs	✓	✓	✓	✓	✓	✓	✓
Laboratory Test Indicators and ECG^l^	✓			✓			
AE^m^ and SAE^n^	✓	✓	✓	✓	✓	✓	✓

a MDASI-OC: MD Anderson Symptom Inventory for Ovarian Cancer.

b PSQI: Pittsburgh Sleep Quality Index.

c PFS-R: Piper Fatigue Scale-Revised.

d PHQ-9: Patient Health Questionnaire-9.

e GAD-7: Generalized Anxiety Disorder-7.

f EORTC QOL-C30: European Organisation for Research and Treatment of Cancer Quality of Life Questionnaire - Core.

g TCM: traditional Chinese medicine.

h OS: overall survival.

i PFS: progression-free survival.

j fMRI: functional magnetic resonance imaging.

k HPA: hypothalamic-pituitary-adrenal.

l ECG: electrocardiography.

m AE: adverse event.

n SAE: serious adverse event.

### Outcomes

#### Primary Outcome

The PNSC score is constructed based on the 4 most relevant symptoms (fatigue, sleep disturbance, distress, and sadness) from the MDASI-OC scale, in accordance with its usage guidelines [24]. Each symptom is rated on an 11-point scale, ranging from 0 (“no symptom”) to 10 (“the most severe imaginable”). The primary efficacy end point of this study is the difference in the PNSC remission rates between the intervention and control groups at 3 months after enrollment. Given that there is no universally accepted evaluation standard for the remission of this specific cluster, “remission” is defined in this protocol through expert consensus. A participant is classified as in “remission” if they meet at least one of the following PNSC-specific criteria: a ≥50% reduction in the total PNSC score relative to the baseline or an absolute PNSC score falling below the threshold of 4 after the intervention. While the primary comparison between the 2 groups will focus on the 3-month mark, longitudinal assessments will be conducted at baseline and at 1, 2, 3, 6, 9, and 12 months after enrollment to monitor symptom dynamics.

#### Secondary Outcomes

##### Pittsburgh Sleep Quality Index

This scale is a widely used instrument comprising 19 self-rated items (which are scored) and 5 nonscored, other-rated items. The 19 scorable items are grouped into 7 components: subjective sleep quality, sleep latency, sleep duration, habitual sleep efficiency, sleep disturbances, use of sleeping medication, and daytime dysfunction. The global Pittsburgh Sleep Quality Index score ranges from 0 to 21, with a higher total score indicating poorer sleep quality [25]. Assessments will be conducted at baseline and at 1, 2, 3, 6, 9, and 12 months after enrollment.

##### Patient Health Questionnaire-9

This scale comprises 9 items that evaluate low mood, loss of interest, sleep disturbance, fatigue, appetite changes, feelings of worthlessness or guilt, concentration difficulties, psychomotor agitation or retardation, and suicidal ideation. Patients will rate the frequency of each symptom over the past 2 weeks on a scale from 0 (“not at all”) to 3 (“nearly every day”). The total score ranges from 0 to 27, with higher scores indicating more severe depressive symptoms [26]. Assessments will be conducted at baseline and at 1, 2, 3, 6, 9, and 12 months after enrollment.

##### Generalized Anxiety Disorder-7 Scale

This scale will be used to screen for and assess the severity of generalized anxiety disorder. It consists of 7 items, each rated on a 4-point scale from 0 (“not at all”) to 3 (“nearly every day”). The total score ranges from 0 to 21, with higher scores indicating more severe anxiety symptoms [27]. Assessments will be conducted at baseline and at 1, 2, 3, 6, 9, and 12 months after enrollment.

##### Revised Piper Fatigue Scale-Chinese Version

This scale is used to assess fatigue. It is a 22-item instrument derived from the original Piper Fatigue Scale, measuring 4 dimensions: behavioral, affective, sensory, and cognitive. Each item is scored on a scale from 0 to 10. The total fatigue score ranges from 0 to 220, and a mean score is calculated by dividing the total score by 22. Higher scores indicate more severe fatigue [28]. Assessments will be conducted at baseline and at 1, 2, 3, 6, 9, and 12 months after enrollment.

##### The European Organisation for Research and Treatment of Cancer Quality of Life Questionnaire - Core Scale

This core instrument for patients with cancer comprises 30 items. Most items are scored on a 4-point scale (1=not at all to 4=very much). Items 29 and 30, which assess overall health and quality of life, use a 7-point scale (1 to 7). The items form 15 scales: 5 functional scales (physical, role, cognitive, emotional, and social), 3 symptom scales (fatigue, pain, and nausea or vomiting), a global health status or quality of life scale, and 6 single items. All scale scores will be linearly transformed to a 0- to 100-point scale. For the functional and global health status scales, a higher score represents a better level of functioning or quality of life. For the symptom scales and single items, a higher score indicates a greater severity of symptoms or problems [29]. Assessments will be conducted at baseline and at 1, 2, 3, 6, 9, and 12 months after enrollment.

##### The TCM Syndrome Pattern Assessment Scale

It is used to collect participants’ relevant symptoms in accordance with the theoretical system of TCM syndrome differentiation. Assessments will be conducted at baseline and at 1, 2, 3, 6, 9, and 12 months after enrollment.

##### Sleep Quality

Portable wrist actigraphy will be used to record patients’ sleep duration. Assessments will be conducted at baseline and at 1, 2, and 3 months after enrollment.

##### Sleep Diary

Sleep will be subjectively monitored using the Sleep Diary Consensus Core Edition [30], which includes bedtime, sleep onset time, number and duration of nocturnal awakenings, and final wake-up time. Assessments will be conducted at baseline and at 1, 2, and 3 months after enrollment.

##### Survival Period

The 1-year OS and progression-free survival (PFS) rates will be determined based on regular imaging assessments conducted during the 1-year follow-up period after randomization.

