### Exploratory Outcomes

#### fMRI Usage

fMRI is an important tool for studying psychoneural mechanisms by detecting blood oxygen level–dependent signals in brain activity and is also an important means for evaluating therapeutic effects [31]. The fMRI will be used to identify the brain regions associated with the PNSCs in ovarian cancer and to assess the changes following treatment. fMRI is planned for 30 randomly selected patients per group, totaling 60 participants. Assessments will be conducted at baseline and 3 months after enrollment.

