#### Survival Outcomes

One-year OS and PFS will be analyzed using the Kaplan-Meier method with log-rank tests. A Cox proportional hazards model will be used to estimate hazard ratios.

A one-sided *P* value of <.03 will be considered statistically significant.

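### OS and PFS rest on imaging that the visit schedule does not contain; with the withdrawal rule, events in patients who leave before day 360 may go unrecorded

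*Protocol article*

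**What the plan says.** Five places in the protocol article bear on this.

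- **Survival Period (Secondary Outcomes):** the 1-year OS and PFS rates "will be determined based on regular imaging assessments conducted during the 1-year follow-up period after randomization". One sentence covers both endpoints.
- **Follow-Up and Table 2:** the section refers the reader to Table 2 for when data are collected. Visits fall on days 30, 60, 90, 180, 270 and 360: "After the completion of treatment, follow-up assessments will be performed every 3 months", and "The total follow-up duration will be 1 year". The row "One-year OS^h^ rate and PFS^i^ rate" is ticked once, at visit 6 (day 360, window 7 days either side). No row covers tumor imaging. The one imaging row is fMRI, at baseline and day 90, and tumor markers are ticked at the same two visits only. AE and SAE recording is ticked at every visit.
- **fMRI Usage:** "The fMRI will be used to identify the brain regions associated with the PNSCs in ovarian cancer". This is brain imaging in 60 patients, not tumor assessment.
- **Survival Outcomes:** "One-year OS and PFS will be analyzed using the Kaplan-Meier method with log-rank tests", with a Cox model for hazard ratios.
- **Data Entry and Modification:** imaging that the protocol calls for is free to participants. The same section withdraws anyone who stops the study intervention or departs from the protocol, and records nothing after the last visit before withdrawal.

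**The concern.** The endpoint definition and the schedule do not agree on how progression is observed. One relies on repeated imaging through the year. The other schedules no such imaging and enters the outcome once, at the end.

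The analysis needs more than a status at one year. Kaplan-Meier, log-rank and Cox methods use the date of each event and assume that censoring is unrelated to the coming event. The withdrawal rule strains that assumption. A patient whose disease worsens may well be the one who stops the granules. Under the rule that patient leaves the study, and Table 2 gives no OS/PFS entry before the one at day 360, which the patient never reaches.

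Basing OS on imaging is a separate slip of wording: a scan can show progression but does not establish that, or when, a patient died.

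At stake is the evidence for a stated secondary objective, the effect on survival. The primary endpoint, PNSC remission at 3 months, does not depend on any of this.

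**Working it through.** The article gives no event count, hazard ratio or power for OS or PFS, so there is no figure to reproduce. The check sets the passages side by side and then adds one illustration.

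**Step 1: what each place supplies**

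| Needed for a time-to-event analysis | Where it would come from | What is there |
|---|---|---|
| Tumor assessments through the year | Survival Period | Stated, no interval given |
| The same assessments in the schedule | Table 2 | No row; fMRI only |
| Progression status and date before day 360 | Table 2 | No tick before visit 6 |
| Date of death | Survival Period | Tied to imaging |
| Death before day 360 | Table 2, AE/SAE rows | Possible route at each visit, until withdrawal |
| Follow-up after stopping the intervention | Data Entry and Modification | None; data end at the last prior visit |

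**Step 2: when the withdrawal rule applies**

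The study intervention lasts 3 months, so stopping it can trigger withdrawal only up to about day 90. The remaining follow-up is then long. A patient whose last visit is day 30 loses 360 − 30 = 330 days, and one whose last visit is day 60 loses 300. After day 90 a patient can still leave through a protocol deviation or under the Dropout Criteria, which include complications and serious adverse events. In each case the day-360 entry is not reached and the AE/SAE rows also end.

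**Step 3: dating error if day 360 were the only assessment (illustration)**

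Assumptions: exponential PFS, with 12-month PFS S between 0.5 and 0.8. This range is assumed and is not taken from the article.

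- Hazard: λ = −ln(S)/12 per month.
- Mean true progression time among those progressing by month 12: 1/λ − 12·S/(1−S).
- Mean delay with one assessment at month 12: 12 minus that mean.
- Mean delay with assessments at months 3, 6, 9 and 12: 3 − [1/λ − 3·s/(1−s)], with s = S^(1/4). Under a constant hazard it is the same in each interval.
- Share of first-year progressions before month 9: (1 − S^(3/4))/(1 − S).

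For S = 0.5: 1/λ = 17.31, so the mean true time is 17.31 − 12 = 5.31 months and the delay is 12 − 5.31 = 6.69 months.

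| S at 12 months | Mean true time (months) | Delay, month 12 only | Delay, 3-monthly | Share before month 9 |
|---|---|---|---|---|
| 0.5 | 5.31 | 6.69 | 1.54 | 81% |
| 0.6 | 5.49 | 6.51 | 1.53 | 80% |
| 0.7 | 5.64 | 6.36 | 1.52 | 78% |
| 0.8 | 5.78 | 6.22 | 1.51 | 77% |

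The delay hardly depends on the assumed rate. It depends on whether day 360 really is the only assessment, which the article leaves open.

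**The case against.** The strongest reply is that the day-360 tick marks when a 1-year rate is read out, not the only time anyone looks for progression. The row label speaks of rates, the Survival Period text places imaging throughout the year, and the data-management section shows that some imaging is foreseen. A condensed article may also leave scan intervals and progression criteria to the full protocol. This stands in part. It rules out saying that early progressions are missed or misdated as a fact. It does not remove the mismatch: if tumor scans are protocol imaging, Table 2 omits them; if the phrase means fMRI, the Survival Period text has no scheduled source. The withdrawal rule is stated text and not an omission.

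Deaths also have a route through the AE/SAE rows. That stands up to withdrawal and not beyond it, so OS is less exposed than PFS. The planned multiple imputation covers secondary endpoints but assumes data missing at random. Its listed inputs are group, baseline values and prognostic covariates, so it would not repair loss driven by progression itself.

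Three stronger readings are tempting and not supported:

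- *Recorded events would all share one date.* A day-360 entry can carry the date of an earlier scan.
- *A count of lost events can be given.* The recurrence figure in the Introduction is background on the disease, not a rate from randomization in this population. The 20% dropout allowance was set for the 3-month endpoint.
- *OS should not be tested because entry requires "Expected survival >1 year".* That is a prognosis at entry, not a guarantee, and the article gives no 1-year OS figure. Few deaths would make the comparison imprecise, not invalid. The Discussion already concedes that 12 months may be too short for long-term OS.

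**Conclusion.** The point holds as an inconsistency between the Survival Period text, Table 2, the withdrawal rule and the survival analysis. As written, a patient who leaves before day 360 has no scheduled OS/PFS entry, so progressions and deaths in such patients may go unrecorded. That loss is plausibly informative, on the assumption that worsening disease is one reason for stopping. How many events are affected cannot be computed from the article.

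Imprecise dating is a conditional second risk. It would average 6.2 to 6.7 months against about 1.5 months with 3-monthly assessment, under exponential PFS of 80% to 50% at 12 months, and only if day 360 is the sole assessment. A 1-year PFS proportion among patients who stay would suffer little; the exposed results are the curve, the log-rank test and the hazard ratio.

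The endpoints are secondary and the primary conclusion is untouched. It should still be corrected before enrollment, because progression dates not collected during the year may not be recoverable.

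**What to change.** Reconcile Survival Period, Table 2, Data Entry and Modification, and Survival Outcomes:

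1. Add a row to Table 2 for progression status with scan date, and vital status with date, at the existing visits 1 to 6.
2. Take progression from scans already being done and date it to the scan, not to the visit.
3. Reword the Survival Period text so that vital status comes from contact or records, and only progression from imaging.
4. Separate stopping treatment from leaving the study for data purposes: continue to collect progression and vital status to day 360 after discontinuation, unless consent is withdrawn. This changes data collection only and leaves decisions on treatment as they are.

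The cost is a little more data collection, mostly at visits that already take place, plus contact with patients who have stopped. No scans are added. The remaining weakness is that the timing of standard-care scans varies between patients, so some imprecision in progression dates will persist. The Results section reports no recruitment as of April 2026, so the change could be in place before the first patient if that is still the case.
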